## Ethics and dissemination

This project will be completed in accordance with the guidelines set out in the Australian National Statement on Ethical Conduct in Human Research.^60^ Ethics approval for the helpline project has been provided by the University of Sydney’s Human Research Ethics Committee (Ethics Approval HE001081). This study does not assign participants to an intervention or treatment but collects data on outcomes following the use of a freely available, and nationwide helpline service. Nonetheless, this study has been designed to minimise and prevent any harm or risks to potential study participants. Adverse events will be monitored throughout the study. Cohort participants will be prompted fortnightly (via text or email according to preferences) to report any adverse events in the preceding 2 weeks via a REDCap survey. Study findings will be disseminated through peer-reviewed research publications and conference presentations, as well as via our partner organisations and involved consumer-advocacy groups. A deidentified, curated data set (excluding data collected from external providers) may be placed in a secure open access repository in accordance with National Health and Medical Research Council (NHMRC) best practice.^61^ In the case of repository data, the chief investigator will ensure the shared data meet’s both the participants’ consent agreement and Multi-Institutional Agreement requirements.

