#### Pre–post cohort study participants (from the helpline)

Two independent cohorts (prehelpline and posthelpline upgrade) will be recruited using consecutive sampling of helpline users presenting with a primary complaint of LBP. At the conclusion of their helpline call, helpline operators will verbally invite eligible users to participate in a research study evaluating the helpline service. Interested individuals will receive an electronic information sheet via an online (email or text) REDCap link. Eligible participants will be adults (≥18 years) who are able to provide informed consent for study participation and have sufficient understanding of written and spoken English to read and complete online forms, and have used the helpline service for advice/management of their LBP. Informed consent will be obtained electronically using REDCap’s e-signature feature, prior to research participation in accordance with the institutional ethics approval. Participants can only be enrolled once in the same research period (ie, in the preperiod or postperiod) but can participate in both. Consenting participants will receive an invitation to complete the baseline, 3-month and 6-month questionnaires via REDCap.

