#### Effectiveness (primary intervention outcome)

The effectiveness of the helpline service will be evaluated at both an individual participant and population (health district) level.

Participant-level effectiveness will be evaluated using a pre–post cohort study. The primary outcome to assess individual effectiveness will be self-reported healthcare use (eg, general practitioner and imaging usage). This will be compared between an independent cohort of participants with a primary complaint of LBP who use the original service, and an independent cohort who use the upgraded service. The primary outcome will be analysed 3 months post service initiation. Cohort participant questionnaires will also capture secondary outcomes including pain intensity,^50^ disability,^51^ quality of life,^52^ the validated single-item physical activity question,^53^ two-item pain self-efficacy,^54^ health confidence score^55^ and acceptability.^41^ Based on historical service volume data from the MHA helpline, we anticipate approximately 50 participants in the preupgrade period and will require a minimum of 208 participants in the postupgrade period to detect an event rate difference of 4 healthcare service utilisations between the preupgrade and postupgrade cohort, with 80% power and 5% type-1 error rate. This is the equivalent of a 40% difference based on an average health service utilisation rate of 10 services per participant over 12 months observed in unpublished work.^56^ Adjusting for a loss to follow-up of 15% in the postupgrade cohort, we will require 245 participants postupgrade to achieve the required 208 completers. Combined with the anticipated preupgrade cohort, the total sample size is 295 participants.

Population effectiveness will be evaluated using aggregated Local Health District data on ED presentations for patients with a complaint of LBP. The analyses will be restricted to the Mid North Coast Local Health District (or relevant hospitals) data corresponding with the location of the media campaign. An interrupted time series design will be used to analyse the monthly change in LBP presentation rates and any associated trend change following the introduction of the media campaign.

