#### Participant-level data

All participant-reported data collection will be conducted externally to MHA by the research team. Data collected from participants will include baseline demographic data (eg, age, sex, education level) from both the preupgrade and postupgrade cohorts, as well as the individuals participating in qualitative interviews or focus groups. For a full list of participant collected data and timepoints, see online supplemental appendix A.

Cohort questionnaires will be administered at baseline (within 10 days of initial helpline service utilisation), 3 and 6 months postinitial service utilisation. All participant collected data will be automatically assigned a unique study identification code and stored and managed using REDCap electronic data capture tools hosted at the University of Sydney.^35 57^ Qualitative data collected during interviews, including transcripts of interviews, will be stored in a password-protected folder in the highly protected SharePoint folder hosted by the University of Sydney. Only designated research team members will have access to this data.

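### The adverse-event recall window equals the prompt interval, so the next fortnightly survey does not ask again about a fortnight whose prompt went unanswered, and the start of the first window is not stated

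*Protocol article*

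**What the plan says.** Under Ethics and dissemination the article states a general aim, "Adverse events will be monitored throughout the study", and then the method: cohort participants are "prompted fortnightly (via text or email according to preferences) to report any adverse events in the preceding 2 weeks via a REDCap survey". This is the only method of adverse-event collection that the article describes. It mentions no look-back past two weeks, no handling of a missed prompt and no start date for the schedule.

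Three other places bear on timing and content:

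- **Pre–post cohort study participants (from the helpline):** "At the conclusion of their helpline call, helpline operators will verbally invite eligible users to participate in a research study evaluating the helpline service". Consent follows electronically, so surveys cannot begin before it.
- **Participant-level data, timing:** "Cohort questionnaires will be administered at baseline (within 10 days of initial helpline service utilisation), 3 and 6 months postinitial service utilisation".
- **Participant-level data, content:** "For a full list of participant collected data and timepoints, see online supplemental appendix A". That appendix is not among the documents at hand.

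**The concern.** A fixed look-back equal to the prompt interval has no overlap. Each survey is the only one in the fortnightly series that asks about its own 14 days. If it goes unanswered, the next survey asks about the following 14 days and the missed period drops out of the series.

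A second gap is possible at the start. Enrolment follows the call, and baseline may be completed as late as day 10. If the fortnightly clock starts at that point, the days just after the call precede the first window. The section on the tailored LBP component anticipates screening and triage for serious pathology, so these are days on which one would want adverse events captured.

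What is at stake is the completeness of the adverse-event record. A period with no answer can look the same as a period with no event, and any count the study reports would then depend partly on how well people responded.

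**Working it through.** The plan gives no figure for adverse-event coverage, so there is nothing of its own to reproduce. The check is arithmetic on the stated schedule.

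**Inputs**

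- Prompt interval 14 days and recall window 14 days (Ethics and dissemination).
- Baseline 0 to 10 days after first helpline use; last questionnaire at 6 months (Participant-level data).
- Assumption: prompts run for the whole 6 months, taken as 26 weeks or 182 days. The article does not state how long they run.
- Assumption: per-prompt response r. The article does not give it, so a range is shown.

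**Number of prompts:** 182 / 14 = 13. If all 13 are answered, 13 × 14 = 182 days are covered and no gap remains.

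**Average uncovered time per participant:** 13 × 14 × (1 − r) days, which is 26(1 − r) weeks. This holds for a given average response however the misses are distributed.

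**Share of participants with no gap, if misses are independent:** r^13.

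| r | Missed prompts, 13(1 − r) | Uncovered days | Uncovered weeks | r^13 |
|---|---|---|---|---|
| 0.95 | 0.65 | 9.1 | 1.3 | 51% |
| 0.90 | 1.30 | 18.2 | 2.6 | 25% |
| 0.85 | 1.95 | 27.3 | 3.9 | 12% |
| 0.70 | 3.90 | 54.6 | 7.8 | 1% |

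**Effect of clustering.** The last column rests on independence and can be far off. Take an average response of 85%. If every miss is intermittent and independent, 12% of participants have no gap. If instead 15% of participants drop out at once and the rest answer everything, 85% have no gap. Average uncovered time is 3.9 weeks in both cases. In the first case most of it could be recovered by a longer look-back; in the second none could.

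**First window.** If the schedule starts on day s after the call, the first prompt falls on day s + 14 and looks back to day s, leaving s days uncovered.

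- s = 0 (anchored to the call): covers days 0 to 14, no gap.
- s = 5: covers days 5 to 19, 5 days uncovered (5 / 182 = 2.7%).
- s = 10 (latest baseline): covers days 10 to 24, 10 days uncovered (10 / 182 = 5.5%).

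**The case against.** The strongest case against the point has four parts.

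1. **The missed prompt did ask.** A reader might infer that harm in a skipped fortnight is never asked about. The documents do not support that. The unanswered prompt asked about it, and appendix A, which lists the collected items, is not shown. The 3- and 6-month questionnaires may already carry an adverse-event item, and reminders or links that stay open may be set out elsewhere. An article commonly leaves such detail to the full protocol. This objection stands, and it limits the point to what the next fortnightly survey asks.

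2. **The early gap is conditional.** No text says that prompts run from enrolment or baseline. The 3- and 6-month questionnaires are timed from first service use, and if the prompts share that anchor the gap is zero. Consent may also come well before day 10. This stands; the gap is possible, not shown.

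3. **The 15% is not a per-prompt miss rate.** It is tempting to read "Adjusting for a loss to follow-up of 15% in the postupgrade cohort" as 85% response at each prompt and to conclude that only 12% of participants would be fully covered. The 15% is a cumulative loss used to size the postupgrade cohort (208 / 0.85 = 244.7, hence 245). It says nothing about response to single prompts. This stands, and the 12% is only one line in a range of assumptions.

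4. **No safety comparison is planned.** A reader might infer a biased comparison of harm between the two cohorts. Adverse events are not a listed outcome in the Effectiveness section or Table 1, and Data analysis plans no between-cohort safety analysis. That unwell people skip prompts is plausible but not documented. This stands, and the comparison argument falls away.

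There is also a fair argument for a short fixed window: it keeps recall length the same for everyone. What survives all of this is the rule that the article does state, a look-back with no overlap. Back-up collection elsewhere would soften its effect but would not change that rule.

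**Conclusion.** The point holds in a narrow form and is minor. As worded, the fortnightly survey does not return to a fortnight whose prompt went unanswered. Up to 10 days after the call could also be missed if the schedule is anchored to enrolment or baseline, which the article leaves open.

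The average uncovered time is 26(1 − r) weeks, assuming prompts run for 6 months. Neither r nor the pattern of misses is given, so no single figure can be defended. Only the part due to intermittent misses is recoverable.

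The schedule does not contradict the aim of monitoring throughout the study, because with complete response the windows cover the whole period. No sample size, primary analysis or planned comparison is affected.

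**What to change.** Word the fortnightly survey to ask about adverse events *since your last completed survey or, if this is your first, since your helpline call*. This closes both gaps for anyone who answers a later prompt, whatever the schedule's anchor. State the anchor as well.

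Check appendix A. If the 3- and 6-month questionnaires have no adverse-event item, add one catch-up question to each, so that a participant who stops answering prompts but completes a questionnaire is still covered.

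The cost is a wording change in one REDCap survey and at most one item in each of two existing questionnaires. The downside is a longer recall period after a missed prompt, and one that varies between participants; recording the date of the previous completed survey lets its length be reported. Participants who leave for good stay uncovered under any wording, so the report should give the response rate per prompt beside the adverse-event counts.

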## Discussion

This protocol describes the implementation and evaluation plan for the helpline project, which may inform future management of LBP in Australia and contribute evidence to guide national implementation. Using an iterative co-design approach, this project aims to develop and evaluate an upgraded helpline that delivers LBP care aligned with stakeholder objectives, while meeting consumer needs. The RE-AIM framework with PRISM extension will enable evaluation of the effectiveness of the intervention and implementation process alongside the contextual factors that influence outcomes. Guided by these frameworks, the research findings are expected to inform the infrastructure required to sustain the helpline service, and the feasibility of the model to support greater call numbers through a broader media campaign.

Anticipated outcomes include improved awareness and uptake of the helpline service, and delivery of evidence-based, patient-centred care that may reduce unnecessary healthcare utilisation. The success of the service is dependent on several factors including the reach of the media campaign to promote awareness, operator fidelity to the codesigned protocol and the ability of the helpline to meet diverse patient needs.

This study also has potential limitations. Promotion and uptake of the service observed across one Local Health District may not be generalisable to other regions of Australia, and increased uptake of the helpline service following the media campaign may not translate to sustained service use once the campaign concludes. To preserve MHA’s aims of providing a freely available nationwide helpline service, the type of design that could be employed to test effectiveness was limited. While a pre–post cohort design allows comparison of service effectiveness before and after the upgrade, the absence of a randomised control group restricts the ability to draw definitive causal inferences.

Finally, individual variability needs and treatment responses among people with LBP mean it is unlikely that the helpline will be equally effective and acceptable for all users. However, implementation evaluation will help identify factors influencing uptake and inform future adaptations to improve reach and acceptability, and effectiveness of the LBP helpline service.
